### **9.6 Procedures for Reporting Any Deviation(s) from the Original Statistical Plan**

Statistical methods could be replaced if it contributes to a more correct and informative analysis. Any deviation(s) from the original statistical plan will be described and justified in the Statistical Analysis Report (SAR) and in the Clinical Study Report (CSR).

### **9.7 Selection of Subjects to be Included in the Analyses**

Following populations will be analyzed:

1. Intention-to-treat population (ITT), which includes every subject who is randomized according to randomized treatment assignment.
2. Per-Protocol population (PP): includes all subjects from ITT population who complete all assessments needed for primary endpoint calculation except subjects with significant protocol deviations.
3. Safety population: Patients who received at least one IP/Placebo dose, according to the prescribed treatment.

## **10 DIRECT ACCESS TO SOURCE DATA/DOCUMENTS**

Source data is the information contained in the original medical records and their certified copies that describe the results of clinical observations, examinations and other activities and allow reproducing the course of a clinical study and evaluate its quality. Source data is contained in the source records (originals or their certified copies) and in electronic form if an electronic data collection system is used.

The Investigator has to authorize monitoring of the study (by the authorized representative of the Sponsor and/or CRO), audits (by the authorized representative of the Sponsor or the company authorized by the Sponsor to conduct audits of the study center) and inspections by the regulatory authorities with direct access to source data and source records including primary documentation and to provide his own time and the time of his staff to work with the monitor, Sponsor's representatives, auditors and regulatory inspectorates to discuss findings and other issues.

## **11 QUALITY CONTROL AND QUALITY ASSURANCE**

### **11.1 Site Monitoring Visits**

Monitoring visits to the study site will be made periodically during the study to ensure that all aspects of the protocol are followed. Source documents will be reviewed for verification of data recorded on the eCRFs. Source documents are defined as original documents, data, and records. The investigator and institution guarantee access to source documents by the Sponsor or CRO and by LEC.

All aspects of the study and its documentation will be subject to review by the Sponsor or designee (as long as blinding is not jeopardized), including but not limited to the Investigator's Binder, study medication, subject medical records, informed consent documentation, documentation of subject authorization to use personal health information (if separate from the informed consent forms), and review of eCRFs and associated source documents.

### **11.2 Protocol deviations**

The Investigator should not deviate from the protocol, except where necessary to eliminate an immediate hazard to study subjects. Should other unexpected circumstances arise that will require deviation from protocol-specified procedures, the Investigator should consult with the Sponsor or designee to determine the appropriate course of action. There will be no deviation from the Inclusion or Exclusion criteria.

The site should document all protocol deviations in the subject's source documents and in the protocol violation record form held in the study master file. In the event of a significant deviation, the site should notify the Sponsor.

### **11.3 Quality Assurance Audits and Regulatory Agency Inspections**

The study site also may be subject to quality assurance audits by the Sponsor or designees. In this circumstance, the Sponsor-designated auditor will contact the site in advance to arrange an auditing visit. The auditor may ask to visit the facilities where laboratory samples are collected, where the medication is stored and prepared, and any other facility used during the study. In addition, there is the possibility that this study may be inspected by regulatory agencies, including those of foreign governments. If the study site is contacted for an inspection by a regulatory body, the Sponsor should be notified immediately. The Investigator and institution guarantee access for quality assurance auditors to all study documents.

### **11.4 Data Monitoring and Quality Control**

NeuroAiD II™ and placebo are provided by Moleac Singapore Pte Ltd and manufactured under the recognized principles of current Good Manufacturing Practice (GMP). This includes that regular audits are conducted by independent health authorities. The GMP standards apply to manufacturing procedures and processes, raw materials, laboratory testing, packaging and distribution. Batches of NeuroAiD II™ are analysed thoroughly by third-party independent laboratories to confirm compliance with international standards, ensuring utmost safety for patients.

Several sources of bias are possible in a study of this type. To overcome these possible biases, particular procedures have been developed. Adherence to these procedures will be monitored at regular meetings of the CRO/Sponsor and the Steering Committee.

- A Data and Safety Monitoring Board will be established including a statistician.
- Due to the nature of the self-report assessments the Investigator will be instructed to rely primarily on information provided by participants.
- Data and logic checks will be conducted to ensure accuracy of the documentation.
- Substantial bias could occur if a low response is achieved from participants, and if there were systematic differences in information about outcomes between cases. These problems will be overcome as far as possible by monitoring responses, ensuring repeated attempts at contact, and allowing flexible convenient assessment times.
- The study will be monitored to ensure data quality and to facilitate entry of participants into the study. An independent Data Safety and Monitoring Board (DSMB) will be established and meet at regular interval as defined by the DSMB Charter (detailed in Section 11.6). Regular monitoring will be done by the Study Manager of CRO and report shared with the Sponsor.

All revisions to the global protocol will be done by the Sponsor and Steering committee (if required) and relevant Ethics Committees will be approached to approve the amendments. If an Amendment substantially alters the study design or increases the potential risk to the participant: (1) the consent form will be revised and submitted to the Ethics Committee(s) for review and approval or favorable opinion; (2) the revised form will be used to obtain consent from participants currently enrolled in the study if they are affected by the Amendment; and (3) the new form will be used to obtain consent from new participants prior to enrolment.

Prior to commencing recruitment of the study participants, the CRO will organize Investigator meeting (Virtual) for training the Investigators and site staff. Training sessions will include training on administering the tests and questionnaires and principles of ICH good clinical practice. Regular meetings with the Investigators and site staff will be maintained by the project team of the CRO to ensure integrity and conduct of the trial according to the Study Protocol.

The study manager of the CRO will provide yearly reports on study progress until completion of the study/termination or discontinuation of the study to the Sponsor (Moleac), Ethics Committees and/or regulatory authorities as per local requirements.

### **11.5 Steering Committee**

The role of the Steering Committee (SC) is to provide oversight of the conduct of the clinical trial and ensures the study is conducted to the required standards. The SC will oversee scientific and practical aspects of the study. The SC will ensure that the study runs in a manner that is safe for study participants and also provides appropriate safety and efficacy data to the Sponsor (Moleac) and to the study investigators. In its safety role, the SC will work with the Data and Safety Monitoring Board (DSMB) established for this clinical trial.

Specific responsibilities of the Steering Committee include, but are not limited to, the following:

- Overall supervision of the clinical trial;
- Monitor recruitment rates and take steps to reduce and minimize deviations from the study protocol, recommend protocol amendments if needed;
- Periodic review of the progress of the clinical trial towards milestones to maximize the likelihood of completion within the agreed time period;
- Work in conjunction with the Data Safety Monitoring Board (DSMB) and review reports on participant safety and data from DSMB;

- Amicably resolve any issues within the research team and the Sponsor regarding the study's data management and monitoring procedures or any recommendations for modifications to the Study Protocol;
- Approve publication and authorship plans suggested by Scientific Advisors and PIs;
- Consider any new external information relevant to the Study.

The SC has the scientific responsibility for this clinical trial and works in conjunction with DSMB who recommends continuation, modification or termination of the study due to safety considerations.

The SC will consist of at least 5 members, including Chair of the SC. The Sponsor (Moleac) will approve all nominations for the SC. SC membership will consist of persons with strong scientific expertise and track record in the field of Traumatic Brain Injury and no conflict of interest. At least three SC members, including the SC Chair or the Chair's designee, will constitute a quorum. The PI will be allowed to attend SC meetings.

The SC will meet prior to the start of the study, and every 6 months thereafter, depending on progress of recruitment and study conduct. The SC may also meet on an *ad hoc* basis as necessary, and/or at the request of the Sponsor (Moleac).

Prior to study initiation a Charter describing in detail SC composition, responsibilities and processes will be signed by the Sponsor (Moleac) and the PI.

#### **11.6 Data Safety Monitoring Board (DSMB)**

An independent Data Safety and Monitoring Board (DSMB) will be established and meet at regular intervals as defined by the DSMB Charter after commencing the trial participants recruitment to ensure safety of the intervention and monitoring Study progress. The role of the Data and Safety Monitoring Board (DSMB) is to safeguard the interests of study participants and to monitor blinded safety data collected in this clinical trial.

Specific responsibilities of the DSMB include, but are not limited to, the following:

- To review the DSMB charters and make recommendation for any changes
- To agree to and evaluate the safety monitoring procedures of this clinical study as proposed by the Study team;
- To make recommendations to the SC regarding any necessary modifications to the Study Protocol and/or to the safety monitoring procedures of this Study;
- To review safety data blinded to treatment allocation, including case reports of suspected ADRs, SUSARs and to request further analyses as necessary;
- Conclude each data review with recommendations to whether the Study should continue without changes, be modified, be analyzed as interim, be terminated, or other optional approaches
- To protect the confidentiality of the study data and the DSMB discussions.

Every effort will be made to reach a consensus within the DSMB and with the Principal Investigator (PI). In case of disagreement on recommended modifications, the SC will make the final decision.

The DSMB will consist of at least three members, with at least one biostatistician, an expert in the field of TBI, and a medical expert with no conflict of interest.

At least 2 DSMB members are required to constitute a quorum.

Prior to study initiation a Charter describing in detail DSMB composition, responsibilities and processes will be signed by the Sponsor and the PI.

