### **4.2 Description of the Measures Taken to Minimize/Avoid Bias**

#### **4.2.1 Randomization**

After consenting to participate in the study and completing the baseline assessment, eligible participants will be randomized to receive either the NeuroAiD II™ (MLC901) or placebo using 1:1 stratified permuted block randomization. This approach will help to stratify by study center, time since injury [1-3 months/4-12 months] and gender. Time since injury between 3 and 4 months will be stratified to 1-3 months. Centralized stratified permuted block randomization will be done using Interactive Web Response System (IWRS). The randomization number will be generated by the system automatically after the investigator enters the patient data into the system. The study team, including the biostatistician, will be un-blinded only after database has been locked.

After the patient signs the ICF at the screening visit, he/she will be assigned the screening number that is assigned in the order of enrolment.

The randomization code will be assigned to each patient that passed the screening and was found eligible.

The randomization code of each patient will be recorded in the source records and the patient's Case Report Form (CRF). If the patient decides to leave the study or does not complete the study for any reason, then his randomization code should not be reused.

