### **8.5 Safety data review by DSMB**

An independent Data Safety and Monitoring Board (DSMB, detailed in Section 11.6) will be established and meet at regular intervals as defined by the DSMB Charter after commencing the trial participants recruitment to ensure safety of the intervention by monitoring blinded safety data collected in this Study. The DSMB will meet prior to the start of the Study and at the projected middle of the study recruitment period, it may also meet on an *ad hoc* basis if necessary.

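### As written, the DSMB is given safety data blinded to allocation and nothing by arm, so it lacks the between-arm comparison that a recommendation to stop for safety needs

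*Protocol*

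**What the plan says.** Three statements set what the board sees.

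- Section 8.5: the board is "to ensure safety of the intervention by monitoring blinded safety data collected in this Study".
- Section 11.6, role: it is "to monitor blinded safety data collected in this clinical trial".
- Section 11.6, duties: "To review safety data blinded to treatment allocation". The same item covers individual reports of suspected reactions and lets the board ask for more analyses.

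The board's remit is wider than that. Section 11.6 has each review end with advice on "whether the Study should continue without changes, be modified, be analyzed as interim, be terminated" or another course, and section 11.5 describes the DSMB as the body "who recommends continuation, modification or termination of the study due to safety considerations".

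On who holds allocation, section 4.2.1 says: "The study team, including the biostatistician, will be un-blinded only after database has been locked". Section 4.7 keeps the blind throughout the trial, allows single patients' codes to be broken in listed circumstances, and has an authorized representative hold the full allocation list. The DSMB does not appear in section 4.7.

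**The concern.** The task and the information supplied for it do not match. Advice to stop because the product is harming patients rests on a comparison of MLC901 with placebo. Read as written, the protocol gives the board data from which that comparison is absent, and it describes no unblinded statistician and no closed report.

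Patient safety is at stake. An imbalance in SAEs, treatment discontinuations or laboratory abnormalities could build up without the one independent safety body seeing it as an imbalance. Table 2.4 lists 36 patients with six months of MLC901 at the trial dose, so experience at this duration is thin.

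**Working it through.** The protocol states no figure on this point that could be reproduced. The check has four steps. All event rates are assumptions, because the protocol gives none for this trial.

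**1. What data without treatment groups can show.** Inputs: 182 randomized, 91 per arm (section 9.2). Suppose 18 patients have an event, so the overall rate is 18/182 = 9.9%. Two-sided Fisher exact test on each possible split:

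| Split of the 18 | Overall rate | Fisher p |
|---|---|---|
| 9 : 9 | 9.9% | 1.00 |
| 12 : 6 | 9.9% | 0.21 |
| 15 : 3 | 9.9% | 0.005 |
| 18 : 0 | 9.9% | 0.000003 |

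The four rows are the same table to a board that sees no arms.

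**2. Whether the overall rate can stand in for the comparison.** It can raise an alarm only against a background rate known from elsewhere. Take 91 patients at mid-recruitment (half of 182; 46 vs 45) and true rates of 16% vs 2%. The expected overall rate is (46 × 0.16 + 45 × 0.02)/91 = 9.1%. Let the alarm sound at the smallest count r with P(X ≥ r) ≤ 0.05 for X ~ Bin(91, background):

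| Assumed background | r | Chance of an alarm |
|---|---|---|
| 2% | 5 | 93% |
| 3% | 7 | 74% |
| 6.9% | 11 | 20% |

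The answer therefore turns on the background. An alarm would also not say which arm caused it.

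**3. What background the protocol supplies.** Section 2.3.2 reports no SAEs in the pilot, with 36 patients on MLC901 and 42 on placebo. For zero events in n, the one-sided 95% upper limit is 1 − 0.05^(1/n). For the 42 placebo patients this is 6.9%; for all 78 it is 3.8%. The protocol thus leaves open the whole range in step 2.

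**4. What data by arm would add at mid-recruitment.** Exact enumeration over both binomials, 46 vs 45 patients, one-sided Fisher test:

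| Assumed rates | Flagged at 2.5% | Flagged at 5% |
|---|---|---|
| 16% vs 2% | 52% | 67% |
| 10% vs 2% | 16% | 28% |

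These figures treat all 91 patients as fully exposed. Many would be only part-way through treatment, so the true values would be lower.

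**The case against.** The strongest reply is that the text is less closed than it looks.

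- **Further analyses.** The duty to review blinded data goes on to let the board ask for more analyses, and it may advise that the trial be analyzed as interim, propose changes to its charter and meet ad hoc. These are real powers, but none of them mentions allocation. A board also has little reason to ask for a split of a total that looks ordinary.
- **Meaning of blinded.** The protocol never says the tables are pooled. Tables by masked arm could fit the wording, and the charter, which is not shown, may provide them. If that is the intention, one sentence settles the point. If the charter instead provides unblinded reports, it conflicts with sections 8.5 and 11.6.
- **A high overall rate is itself a signal.** This stands. For 16% vs 2% with a background known to be 2%, the overall count alarms more often (93%) than by-arm review at one-sided 5% (67%). It depends on knowing the background, and it cannot attribute the excess to MLC901.
- **Prior exposure.** Table 2.4 also lists 146 patients on MLC901 at this dose for one to three months (15 + 131) and 1838 on the precursor MLC601. This lowers the prior concern but does not replace a comparison within the trial.

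A reader might infer that no allocation can be known before database lock. The documents do not support that: the lock rule in section 4.2.1 covers the study team, and section 4.7 allows individual codes to be broken earlier, including for safety. A code break for one patient is still not a comparison of arms.

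**Conclusion.** The point holds as a gap between task and information. Three statements limit the board to blinded data, two sections let it advise on stopping for safety, and none gives it data by arm. On data without treatment groups, an imbalance as strong as 15:3 cannot be told from 9:9.

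A reader might go further and conclude that the board could detect no harm at all. That is not supported: single striking cases and a clearly raised overall rate remain visible, and the board can ask for more. Nor would data by arm be a sensitive safeguard at mid-recruitment. It would catch only large excesses, and the detection figures rest on assumed rates and full exposure.

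The conclusion assumes that blinded means without treatment groups, and that the charter does not say otherwise. The change should be made, but the trial does not fail without it.

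**What to change.** - In sections 8.5 and 11.6, state that the DSMB receives closed-session safety tables by coded arm (A/B), with the key released on its request.
- Have the coded export produced by the holder of the allocation list described in section 4.7, or by another person outside both the study team and the voting board. A voting member who built the tables from the list would be unblinded from the start.
- Align sections 4.2.1 and 4.7 with this route, so that the Sponsor, Steering Committee, study team and sites stay blinded.

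No stopping threshold is proposed.

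The cost is some protocol and charter wording and one restricted export from the IWRS. The downside is that a firewall must be kept around the closed tables, for a review that at mid-recruitment can show only large differences.

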## **12 ETHICS**

This study will be conducted in accordance with the ethical principles that have their origins in the Declaration of Helsinki. The study protocol and any subsequent amendment(s) will be submitted to the Ethics Committee. The study will be conducted in compliance with the protocol, GCP regulations and the applicable regulatory requirements.

The regulatory application or submission for regulatory approval will be made by the Sponsor as required by law of Russian Federation. Regulatory considerations concerning current study are detailed in Section 2.6.

### **12.1 Approval by Ethics Committee**

The Sponsor or designee will supply relevant documents for submission to the respective Ethics Committee (LEC, Local Ethics Committee) or for the protocol's review and approval. This protocol, the Investigator's Brochure, a copy of the Informed Consent Form, and, if applicable, subject recruitment materials and/or advertisements and other documents required by all applicable laws and regulations, must be submitted to a LEC for approval. The written approval by the LEC of the protocol and subject informed consent must be obtained and submitted to the Sponsor or designee before commencement of the study (i.e., before shipment of the sponsor-supplied drug or study specific screening activity). The approval must refer to the study by exact protocol title, number, and version date; identify versions of other documents (e.g., Informed Consent Form) reviewed; and state the approval date.

Sites must adhere to all requirements stipulated by the respective ethics committee.

### **12.2 Subject Information and Informed Consent**

Written consent documents will embody the elements of informed consent as described in the Declaration of Helsinki and the ICH Guidelines for GCP and will be in accordance with all applicable laws and regulations. The Informed Consent Form and subject information sheet will describe the planned and permitted uses, transfers, and disclosures of the subject's personal and personal health information for purposes of conducting the study. The Informed Consent Form and the subject information sheet further explain the nature of the study, its objectives, and potential risks and benefits, as well as the date informed consent is given. The Informed Consent Form will detail the requirements of the participant and the fact that he or she is free to withdraw at any time without giving a reason and without prejudice to his or her further medical care.

The Investigator is responsible for the preparation, content, and LEC approval of the Informed Consent Form. The Informed Consent Form and subject information sheet must be approved by both the LEC and the Sponsor prior to use.

The Informed Consent Form and subject information sheet (if applicable) must be written in a language fully comprehensible to the prospective subject. It is the responsibility of the investigator to explain the detailed elements of the informed consent form and subject information sheet (if applicable) to the subject. Information should be given in both oral and written form whenever possible and in the manner deemed appropriate by the LEC.

The subject must be given ample opportunity to: (1) inquire about details of the study and (2) decide whether or not to participate in the study. If the subject determines he or she will participate in the study, then the Informed Consent Form must be signed and dated by the subject, or the subject's legally acceptable representative, at the time of consent and prior to the subject entering into the study. The subject or the subject's legally acceptable representative should be instructed to sign using their legal names. The investigator must also sign and date the informed consent form at the time of consent and prior to subject entering into the study.

Once signed, the original Informed Consent Form and subject information sheet will be stored in the Investigator's site file. The investigator must document the date the subject signs the informed consent in the subject's medical record. Copies of the signed Informed Consent Form and subject information sheet shall be given to the subject.

All revised Informed Consent Forms must be reviewed and signed by relevant subjects in the same manner as the original informed consent. The date the revised consent was obtained should be recorded in the subject's medical record, and the subject should receive a copy of the revised Informed Consent Form.

